## Abstract

**Background:**

Group reminiscence therapy is a brief and structured intervention in which participants share personal past events with peers. This approach has been shown to be promising for improving wellbeing and reducing depressive symptoms among institutionalized older adults. However, despite the considerable interest in reminiscence group therapy, controlled studies to determine its specific benefits as compared to generic social interactions with peers (group conversations about everyday subjects) are still lacking.

**Methods/Design:**

We have designed a randomized controlled trial aimed at comparing the effects of group reminiscence therapy with those of group recreational activity on the psychological wellbeing of an institutionalized sample of older adults. The study includes two groups of 20 hospitalized elderly participants: the experimental group and the control group. Participants included in the experimental group will receive six sessions of group reminiscence therapy, while the control group will participate in a recreational group discussion. A repeated-measures design will be used post-intervention and three months post-intervention to evaluate changes in self-reported outcome measures of depressive symptoms, self-esteem, life satisfaction, and quality of life from baseline.

**Discussion:**

The protocol of a study aimed at examining the specific effects of group reminiscence therapy on psychological wellbeing, depression, and quality of life among institutionalized elderly people is described. It is expected that the outcomes of this trial will contribute to our knowledge about the process of group reminiscence, evaluate its effectiveness in improving psychological wellbeing of institutionalized individuals, and identify the best conditions for optimizing this approach.

**Trial registration:**

This trial was registered with ClinicalTrials.gov (registration number: NCT02077153) on 31 January 2014.

## Background

It has been estimated that in Europe the elderly population (aged over 65) will increase significantly over the next few decades, with the number of seniors reaching over 150 million by 2060. An even more dramatic growth will be experienced in the over-eighties population, which will triple to more than 60 million individuals by the same year [1].

As a consequence of this demographic shift, the percentage of dependent seniors in need of institutional care in nursing homes will increase proportionally. A major clinical and policy challenge posed by residential care is the high prevalence of mental health problems among institutionalized elderly individuals. Therefore, the development and provision of effective mental health care interventions for nursing home residents has become an important goal for researchers and practitioners [2].

### Reminiscence therapy

Reminiscence therapy has been proposed as a potentially effective strategy to improve quality of life and psychological wellbeing for elderly nursing home residents [3]. This approach involves the recollection, review, and re-evaluation of personally experienced past events. It is believed that reminiscence therapy can help elderly individuals by increasing self-acceptance, providing perspective, and enabling the resolution of past conflicts [4, 5].Three main reminiscence modalities are identified in literature: simple reminiscence, life review, and life-review therapy [6, 7]. The first approach works best with older adults who have relatively good mental health and involves the simple recollection of positive autobiographical events, with the goal of fostering positive emotions. In contrast, life review focuses on both positive and negative memories, encompassing the entire life span. The goal of this intervention is to perform a critical analysis of one’s life history and achieve ego integrity [8]. Finally, life-review therapy is aimed specifically at elderly persons suffering from mental conditions, with particular applicability to patients with a diagnosis of depression. By assisting patients to reframe negative memories in a positive way, life-review therapy focuses on restructuring beliefs and on building self-efficacy and coping skills. However, it should be noted that the definition of these modalities is often merged [7]. The structure and format of reminiscence interventions also vary considerably across studies. Generally, reminiscence treatments last six weeks or longer, and include at least one or two sessions per week, each session lasting between one and two hours. Moreover, reminiscence activities can be performed either one-to-one or in groups. Reminiscence groups include between six and eight participants and are usually managed by institutional care workers or psychologists.

The effectiveness of reminiscence therapy has been investigated by several meta-analyses [6, 9–13]. Pinquart *et al*. [13] analyzed 57 controlled studies, of which eight compared reminiscence with a control condition. Reminiscence was associated with a large effect size (d =1.00), comparable with cognitive behavioral therapy (CBT). These findings lead the authors to conclude that reminiscence and CBT are effective modalities of treatment for depression in older adults. A more recent review by Pinquart and Forstmeier [6] aggregated results of 128 selected studies. Findings showed that reminiscence interventions produced small to moderate improvements of depressive symptoms (g =0.57) and of other indicators of mental health, such as ego integrity (g =0.50), purpose in life (g =0.73), and death preparation (g =0.52). In addition, it was found that improvements of depression were greater than improvements of positive mental health and cognitive performance. With respect to moderator variables, results of this meta-analysis showed that life-review therapy had stronger effects on depression than either life review or simple reminiscence. However, this effect was explained by higher levels of depression symptoms in life-review patients at pre-test. There was no significant difference between the one-to-one and group formats. In addition, the number of sessions had no moderating effects.

In summary, the findings of previous meta-analytic studies indicate that reminiscence therapy is a promising non-pharmacological approach to improve mental health in elderly individuals. However, more randomized controlled trials are needed to assess the effectiveness of this strategy and its specific benefits for institutionalized seniors [14].

## Methods/Design

### Aim of the study

Based on the need for further randomized controlled trials in this area, the present study aims at assessing the effects of group reminiscence on psychosocial wellbeing in institutionalized, non-demented elderly individuals. First, we will examine the specific effects of simple reminiscence as compared to a placebo intervention in which participants are engaged in everyday conversations (discussion of current events). The findings of previous meta-analyses are inconclusive on this issue. The review carried out by Bohlmeijer *et al*. [9] found no significant differences between studies that used an active placebo and those that used a wait-list condition. In contrast, the Pinquart and Forstmeier meta-analysis [6] observed larger improvements in positive wellbeing if the control condition received no intervention as compared to standard conversation, indicating that socialization activities can also bring about positive emotional states.

Second, we intend to assess the impact of reminiscence on a broad range of psychosocial outcome indicators, including depression symptoms, positive wellbeing (self-esteem, life satisfaction), and quality of life. Since we aim to evaluate the specific effectiveness of simple reminiscence by comparing it to conversation on current events, clinically depressed residents will not be included in the trial. More specifically, we will examine four hypothesis. Hypothesis one is that we expect an improvement of self-esteem, evaluated through the Rosenberg Self-Esteem Scale [15], in the experimental group by the end of the protocol when compared to the control group. Hypothesis two is that we expect an increase of life satisfaction, evaluated through the Life Satisfaction Index [16], in the experimental group by the end of the protocol when compared to the control group. Hypothesis three is that we expect an increase of the perceived quality of life, evaluated through the WHOQOL-Old Scale [17], in the experimental group by the end of the protocol when compared to the control group. Finally, hypothesis four is that we expect a decrease of depressive symptoms, measured through the Geriatric Depression Scale (GDS) [18], in the experimental group by the end of the protocol when compared to the control group. Further, we will assess whether these expected improvements in mental health and psychological well-being are maintained during a three-month follow-up period.

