### Participants and inclusion criteria

The present study is a randomized controlled trial, which involves two groups of participants living in the ageing research and treatment center of Istituto Auxologico Italiano: the experimental group (EG) and the control group (CG). The total sample size is 40 participants, or 20 per group (sample size estimation details are reported in the following section).

In order to be included in the study, individuals have to meet the following criteria: be 65 years of age or older; have an absence of major depressive symptoms, as indicated by a score lower than 17 on the GDS [18]; have an absence of cognitive impairment, as indicated by a score greater than 21 on the Mini Mental State Examination that corresponds to mild dementia [19]; and are not currently receiving any other psychological treatment for improving wellbeing. Both males and females will be included (Figure 1).

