**CONSORT flow diagram.**

### Sample size calculation

The number of participants was calculated in order to have a sufficient size to prove the effect of training, reducing type two (false negative) statistical errors. The limit of 0.05 will be used for type one errors (false positive).

Sample size calculation used an assumption that participants in the experimental group would report improvements, based on outcome over time, and that these effects would differ from those achieved in the control group. As noted in the introductory section, previous evaluations of this kind of reminiscence intervention have produced moderate effect sizes [20, 21]. Accordingly, we estimated a sample size for a moderate treatment effect over time. We calculated sample size by using a repeated-measures analysis of variance across time (pre-post) with an α level set at 0.05 (two-tailed), statistical power level (1-β) of 0.80, and an estimate of correlation among repeated measures of 0.5. The calculation, based on GPower 3 (Heinrich-Heine-Universität, Düsseldorf, Germany) [22], led us to estimate minimum sample size of 40 participants (or 20 per group).

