#### Outcome measures

For the assessment of group reminiscence outcome, we will administer several questionnaires at baseline, post-intervention, and three months post-intervention. The Life Satisfaction Index ([16]; Italian validation [24]) is a questionnaire used to assess satisfaction of life that includes 20 items with three possible answers of ‘yes’, ‘no’, or ‘do not know’. The Life Satisfaction Index covers feelings of wellbeing among older people to identify ‘successful’ aging; it includes components like joy, resilience, comparison between desired and achieved goals, positive view of the self, and mood tone. It is assessed by evaluating the individual’s way of facing daily activities, finding life meaningful, reporting a feeling of success, and a positive self-image. The Rosenberg Self-Esteem Scale ([15]; Italian validation [25]) is a questionnaire with 10 items in which the respondents will be asked to reflect on their current feelings. Self-esteem is measured through four-point Likert scales from ‘strongly disagree’ to ‘strongly agree’. The scale score ranges from 0 to 30, with a higher score indicating higher self-esteem. Scores between 15 and 25 are within the normal range and scores below 15 indicate low self-esteem.

The WHOQOL-Old [17] questionnaire measures the perceived quality of life, with 24 items assessing various aspects of the quality of life, using five-point Likert scales. The scale is split into six subscales which explore different aspects: sensory abilities, autonomy, past, present and future activities, social participation, death and dying, and intimacy. The Geriatric Depression Scale ([18]; Italian adaptation [26]) evaluates the presence of depressive symptoms among older adults. It is composed of 30 items with possible answers of ‘Yes’ or ‘No’. One point is given to each answer based upon a scoring grid, and then the cumulative score is calculated. The simplicity of this scale is appropriate for older adults. The Reminiscence Function Scale [27] is only for the experimental condition. This questionnaire includes 43 items investigating the main functions and purposes of the reminiscing activity over the life course using six-point Likert scales. Seven factors have been identified: boredom reduction, death preparation, identity and problem-solving, conversation, intimacy maintenance, bitterness revival, and teach and inform.

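### Four unranked efficacy hypotheses at the end of the intervention, with no primary outcome named and a sample size tied to none of them

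*Protocol article*

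**What the plan says.** In the protocol article, Aim of the study, the efficacy questions are introduced with "More specifically, we will examine four hypothesis". They share one form:

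- "Hypothesis one is that we expect an improvement of self-esteem, evaluated through the Rosenberg Self-Esteem Scale [15], in the experimental group"
- "Hypothesis two is that we expect an increase of life satisfaction, evaluated through the Life Satisfaction Index [16], in the experimental group"
- "Hypothesis three is that we expect an increase of the perceived quality of life, evaluated through the WHOQOL-Old Scale [17], in the experimental group"
- "hypothesis four is that we expect a decrease of depressive symptoms, measured through the Geriatric Depression Scale (GDS) [18], in the experimental group"

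Each is a comparison with the control group at the end of the intervention. The same section then asks whether the expected gains persist over three months.

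Outcome measures describes the scales without ranking them. Sample size calculation states "The limit of 0.05 will be used for type one errors (false positive", and gives two-tailed 0.05, power 0.80, a correlation of 0.5 among repeated measures and a moderate effect. It arrives at 40 participants, 20 per group, and refers only to outcome over time, with no scale named. Trial analysis plans analysis of variance to judge the overall significance of improvement across the outcome measures. The article nowhere gives a primary outcome, a testing order or a joint rule for success.

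**The concern.** The choice of primary outcome is a protocol decision, because it determines what the trial is sized for and which result answers its question. Here four hypotheses stand side by side under one type I limit.

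If the scales disagree, which is quite possible with 20 per arm, nothing in the article says which one carries the conclusion. The Abstract and Discussion frame the aim as effectiveness for psychological wellbeing, a construct to which any of the four scales could be said to speak. A reader of the results could not tell a planned main finding from the most favourable of four. The power statement has the same gap: 0.80 applies to an unnamed outcome.

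**Working it through.** **Inputs from the article:** four hypotheses at the end of the intervention (Aim of the study); two-tailed alpha 0.05, power 0.80, correlation over time 0.5, N = 40 at 1:1 (Sample size calculation).

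**Inputs assumed:** no true effect on any scale; each scale tested once at 0.05; between-scale correlation r from 0 to 0.7. The article gives no between-scale correlation. Its 0.5 is a correlation over time within a scale.

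**1. The plan's own figure.** For the group-by-time interaction with m = 2 occasions, the G*Power noncentrality is λ = N·m·f²/(1 − ρ). The article gives no number for a moderate effect, so take f = 0.25 as an assumption.

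- N = 34: λ = 34 × 2 × 0.0625/0.5 = 8.5, power 0.81. This is the smallest even N that reaches 0.80.
- N = 40: λ = 40 × 2 × 0.0625/0.5 = 10, power 0.87.
- N = 40 at power 0.80 exactly corresponds to f of about 0.227.

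The 40 is thus not reproduced with f = 0.25. Since the effect size is not stated as a number and 40 exceeds 34, this is not shown to be an error, and the point here does not depend on it. What matters is that no scale enters the calculation.

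**2. At least one significant result, either direction.** If the tests are independent: 1 − (1 − 0.05)⁴ = 1 − 0.8145 = 0.185. With equal correlation between the four test statistics (simulation, 1,000,000 normal vectors):

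| r | 0 | 0.3 | 0.5 | 0.7 |
|---|---|---|---|---|
| Either direction | 18.5% | 17.4% | 15.5% | 13.0% |
| Direction of benefit only | 9.6% | 8.7% | 7.8% | 6.5% |

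Simulated t-tests with 20 per arm agree for the first row: 18.3% (r = 0), 15.3% (r = 0.5), 13.4% (r = 0.7). At r = 0.8 the either-direction figure is 11.4%.

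**3. At least one false finding of benefit.** All four hypotheses state a direction. A two-sided 0.05 test puts 0.025 in that direction, so with independence 1 − (1 − 0.025)⁴ = 0.096. The second row of the table gives the correlated cases. One test would give 2.5%.

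**4. Cost of controlling the error over all four.** Holm's first step tests the smallest p-value at 0.05/4 = 0.0125. For a post-intervention comparison of two means with 20 per arm (38 degrees of freedom), the noncentrality is d·√(20/2):

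| Two-sided alpha | d for 80% power | Power at d = 0.91 |
|---|---|---|
| 0.05 | 0.91 SD | 0.80 |
| 0.0125 | 1.10 SD | 0.60 |

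On the interaction scale the result is the same: at f = 0.227 and N = 40, power falls from 0.80 to 0.60. At f = 0.25 it falls from 0.87 to 0.70.

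**The case against.** The strongest reply is that a multiplicity procedure is commonly left to a statistical analysis plan, which is not shown, and that a journal article condenses. That stands for the procedure: its absence is no finding. It does not cover the primary outcome, which belongs in the protocol, and here the article positively sets up four parallel hypotheses.

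Testing each scale at 0.05 is also an inference. The 0.05 appears in the sample size section and is called neither per-test nor family-wise. The wording in Trial analysis about overall significance could hint at a global test, though none is defined. It would therefore go too far to say that the plan breaks a promise of family-wise control. Nor does the article say that success on one scale would establish better wellbeing, since each hypothesis concerns its own construct.

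Four stronger readings might tempt a reader, and the article does not support them:

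- **Eight tests, counting three months.** Aim of the study frames follow-up as maintenance of gains already seen, not as four further hypotheses.
- **Extra tests from the quality-of-life scale.** "The scale is split into six subscales which explore different aspects" describes how the instrument is built. No subscale tests are planned.
- **Depression cannot be a primary outcome because entry requires absence of major symptoms,** "as indicated by a score lower than 17 on the GDS". Scores of 0 to 16 remain possible. The review cited under Reminiscence therapy found larger gains in depression than in positive mental health. Its remark about pre-test levels explains a difference between modalities.
- **A 13% to 19% risk of falsely claiming benefit.** That range counts results in either direction. The risk for benefit alone is about half.

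**Conclusion.** The point holds in a limited form. The article fixes four co-equal hypotheses, names no primary outcome and attaches its sample size to none of them. An unseen analysis plan does not excuse this.

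The size is conditional on one two-sided 0.05 test per scale, no true effect on any scale, and between-scale correlations assumed between 0 and 0.7. On those terms at least one significant result has probability of about 13% to 19%, and at least one false finding of benefit about 6.5% to 9.6%. The latter is roughly 2.6 to 3.8 times the 2.5% of a single test (6.5/2.5 and 9.6/2.5). Higher correlations would lower the figures. This is an inexpensive improvement to the plan and does not invalidate the trial.

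**What to change.** **Preferred.** Before the data are examined, name one of the four total scores at post-intervention as the primary outcome, state that the sample size calculation refers to it, and make the other three secondary. The choice among the four is the investigators' to make and justify. This is a change of wording, with N unchanged and no loss of power for the primary outcome. Trial status reports recruitment and data collection still in progress, so the choice could still be made at that time.

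**If all four are to stay co-equal.** Apply Holm's procedure at family-wise 0.05 to the four total scores at post-intervention, and say so in the protocol. The cost is power: in a simple post-intervention comparison with 20 per arm, power at 0.91 SD drops from 0.80 to 0.60 at Holm's first step. State this loss next to the sample size.

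**In either case.** Add one sentence saying that the three-month comparisons are supportive. This is close to how the aims already present them and costs nothing.

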### Participants and inclusion criteria

The present study is a randomized controlled trial, which involves two groups of participants living in the ageing research and treatment center of Istituto Auxologico Italiano: the experimental group (EG) and the control group (CG). The total sample size is 40 participants, or 20 per group (sample size estimation details are reported in the following section).

In order to be included in the study, individuals have to meet the following criteria: be 65 years of age or older; have an absence of major depressive symptoms, as indicated by a score lower than 17 on the GDS [18]; have an absence of cognitive impairment, as indicated by a score greater than 21 on the Mini Mental State Examination that corresponds to mild dementia [19]; and are not currently receiving any other psychological treatment for improving wellbeing. Both males and females will be included (Figure 1).

**Figure 1 Fig1:**
[figure not shown]
**CONSORT flow diagram.**

### Sample size calculation

The number of participants was calculated in order to have a sufficient size to prove the effect of training, reducing type two (false negative) statistical errors. The limit of 0.05 will be used for type one errors (false positive).

Sample size calculation used an assumption that participants in the experimental group would report improvements, based on outcome over time, and that these effects would differ from those achieved in the control group. As noted in the introductory section, previous evaluations of this kind of reminiscence intervention have produced moderate effect sizes [20, 21]. Accordingly, we estimated a sample size for a moderate treatment effect over time. We calculated sample size by using a repeated-measures analysis of variance across time (pre-post) with an α level set at 0.05 (two-tailed), statistical power level (1-β) of 0.80, and an estimate of correlation among repeated measures of 0.5. The calculation, based on GPower 3 (Heinrich-Heine-Universität, Düsseldorf, Germany) [22], led us to estimate minimum sample size of 40 participants (or 20 per group).

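### The 80% power claim is not justified for reminiscence versus conversation: the 'moderate' effect has no stated value, metric or comparator, and 20 per arm needs about 0.91 SD

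*Protocol article*

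**What the plan says.** Under 'Aim of the study' the protocol article sets its first objective: "we will examine the specific effects of simple reminiscence as compared to a placebo intervention in which participants are engaged in everyday conversations". 'Trial design' and 'Control group' confirm that the control is an active discussion group on current events.

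'Sample size calculation' assumes that the experimental group improves over time "and that these effects would differ from those achieved in the control group". The size of that difference comes from the literature: "previous evaluations of this kind of reminiscence intervention have produced moderate effect sizes [20, 21". The section then says "Accordingly, we estimated a sample size for a moderate treatment effect over time" and states the design "with an α level set at 0.05 (two-tailed), statistical power level (1-β) of 0.80", with a pre-post repeated-measures analysis of variance and a correlation of 0.5. The result is 40 participants, 20 per group. The effect has no numeric value or metric, and no comparator is named for the studies it comes from.

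The section refers back to the introduction. There, 'Reminiscence therapy' gives g = 0.57 for depressive symptoms from a review of 128 studies and describes it as small to moderate. It also gives d = 1.00 from an earlier review, described as large. It adds that "improvements of depression were greater than improvements of positive mental health and cognitive performance". Neither figure is reported as an effect against conversation.

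On the comparator, 'Aim of the study' cites two reviews and calls their findings inconclusive. One found no significant difference between active-placebo and wait-list studies. The other "observed larger improvements in positive wellbeing if the control condition received no intervention as compared to standard conversation".

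**The concern.** Power depends on the assumed effect, and the effect that matters here is what reminiscence adds over peer conversation. If the conversation group also improves, the between-arm difference is smaller than the difference against no intervention. The protocol allows for this when it notes that socialising can itself produce positive emotional states. The sample-size section nevertheless takes a general reminiscence effect without naming its comparator and makes no allowance for an active one.

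What is at stake is how far the stated "statistical power level (1-β) of 0.80" can be relied on for the trial's main question. A reader who takes it at face value would credit a trial of 40 with more ability to detect a specific benefit than the protocol's own figures support.

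**Working it through.** **Inputs.** From 'Sample size calculation': n = 20 per arm, two-sided α = 0.05, two time points, correlation ρ = 0.5, target power 0.80. From 'Reminiscence therapy': g = 0.57. The documents give no numeric planning effect and no figure for reminiscence versus conversation.

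**Method.** With two arms and two time points, the arm-by-time interaction is equivalent to a two-sample t-test on change scores.
- SD of change = √(2(1 − ρ)) = √(2 × 0.5) = 1 baseline SD.
- Let D be the between-arm difference in mean change, in SD units. The noncentrality is D × √(n/2) = D × √10 = 3.162 D, with 38 degrees of freedom and critical t = 2.024.
- In effect-size-f terms, f = D/4 and λ = N·m·f²/(1 − ρ), with N = 40 and m = 2.

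**Step 1: the plan's own figure.** The 40 cannot be reproduced exactly, because 'moderate' has no value. If it means the conventional f = 0.25 (my assumption):
- At N = 34, λ = 34 × 2 × 0.0625/0.5 = 8.5 and power is 80.7%, so the minimum would be 34.
- At N = 40, λ = 10 and power is 86.9%.
- On this scale f = 0.25 means D = 4 × 0.25 = 1.0 SD.

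**Step 2: the effect that gives 80% with 20 per arm.** Solving for power 0.80 gives D = 0.909 SD, or f = 0.227.

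**Step 3: the introduction's figure.** Reading g = 0.57 as D = 0.57 SD (an assumption about the metric), f = 0.57/4 = 0.1425 and the noncentrality is 0.57 × 3.162 = 1.80. Power is 42%. Reaching 80% would need 50 per arm. If the analysis adjusted for baseline (residual SD √(1 − 0.25) = √0.75), power would be 53%. None of these figures includes a discount for the active control.

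**Step 4: power over a range, 20 per arm, change-score test.**

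| D (SD of change) | Power |
|---|---|
| 1.00 (f = 0.25) | 87% |
| 0.91 | 80% |
| 0.57 | 42% |
| 0.50 | 34% |
| 0.43 (0.75 × 0.57) | 26% |

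**Step 5: how a smaller effect against conversation would act.** Starting from the effect that gives exactly 80%, losses of 10%, 25% and 50% leave power of 71%, 56% and 29%. These fractions are illustrative; the documents supply none.

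**The case against.** The strongest reply is that no mismatch of comparators has been shown. The planning effect is attributed to references 20 and 21, whose values and control conditions are not given in the article, and they may have used active controls. The g = 0.57 comes from a different source; the sample-size section's pointer to the introduction suggests a link but does not establish one. This stands, so the point is limited to a missing justification.

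A reader might infer that the protocol itself reports smaller gains against conversation. That is true of one of two reviews, and only for positive wellbeing. The other found no significant difference by control type. The protocol defines positive wellbeing as self-esteem and life satisfaction and lists quality of life separately, so this evidence bears directly on two of the four hypotheses. No comparator evidence is given for depression. The introduction's other pooled figures, such as g = 0.50 for ego integrity and g = 0.73 for purpose in life, also fit a 'moderate' label.

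A reader might also infer that the 80% does not apply to the between-arm comparison at all. The documents do not support that: the calculation explicitly assumes a difference from the control group, and its 80% is conditional on the assumed effect.

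Nor does it follow that a non-significant result is the likely outcome. From the 80% base, power drops below 50% only after a loss of about 30% (D = 0.64 SD). From f = 0.25, even a 10% loss leaves 79%. The 42% at g = 0.57 reflects the unstated size and metric of the effect, not a discount for the comparator.

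Finally, confidence-interval reporting and rules for interpreting a null result are commonly left to an analysis plan, and this point does not depend on them.

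**Conclusion.** The concern holds as a gap in justification. The 80% power is not supported for reminiscence versus conversation, because the effect behind it has no value, metric or comparator. With 20 per arm it requires about 0.91 SD in change. The introduction's pooled figure for depressive symptoms gives about 42%, before any allowance for the active control. The effect may be smaller again for self-esteem and life satisfaction, but the evidence cited for that is divided.

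These sizes rest on the stated design (pre-post, ρ = 0.5, two-sided 0.05, 20 analysed per arm) and, for the 42%, on reading g = 0.57 as a between-arm difference in change in baseline SD units. That the references used a different kind of control, or that the trial will probably miss a real benefit, is not established.

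**What to change.** Keep N = 40 and revise 'Sample size calculation' as follows:
- State the assumed effect as a number, with its metric (f, or a difference in change in SD units) and the comparator in the studies it comes from. If no figure against a conversation control is available, say so.
- Replace the 80% claim with the detectable difference: 20 per arm gives 80% power for about 0.91 SD in change, at correlation 0.5 and two-sided 0.05.
- Add power over a range of effects, for example 87% at 1.0 SD, 42% at 0.57 SD, 34% at 0.50 SD and 26% at 0.43 SD.

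This is a rewording only, with no extra participants, staff or procedures. The downside is that the stated power looks less favourable.
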